## Recruitment {15}

### Participant recruitment

We aim to recruit 46 participants (23 individuals in each arm) diagnosed with PCOS using online advertising and posters posted through Motazadi Gynecology and Obstetrics Hospital, healthcare establishments, physician offices, pharmacies, and laser clinics. These people will come from the public population. One of the researchers involved in the study will do the recruitment. Participants will be asked to visit Fatahi Clinics where the screening will be performed. At the first visit, the screening will be carried out by a dietitian and an obstetrician-gynecologist to determine eligible patients according to the inclusion criteria and have a detailed explanation about the study, as well as provide written informed consent.

## Assignment of interventions: allocation

### Sequence generation {16a}

#### Randomization

During the first visit, participants will be randomized to either the PLCD or the KD. Randomization will be conducted by an investigator who is not involved in obtaining or entering participants’ data. The samples will be included in the study with informed consent using a random block method of 6 that will be created by the website https://www.sealedenvelope.com.

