#### Concealment mechanism {16b}

The following will be considered in the implementation of the random assignment process: (a) one English letter is assigned to each of the groups: A to the PLCD group, B to the KD group; (b) a sequence for the sample size 23 will be created; (c) for the concealment process of random allocation, 23 non-transparent envelopes and cards (as much as the total sample size) will be prepared. Inside each envelope, 6 cards will be placed in the order of the sequence in each block. Block numbers will be written on each envelope. The name of the desired group will be written on each card in sequence.

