#### Implementation {16c}

The investigator who collects the information is unaware of the type of allocation of the samples to the study groups. The participants will be enrolled to the study by both a dietitian and an obstetrician-gynecologist according to the eligible criteria. Then, the dietitian will randomly stratified participants to receive either PLCD or KD.

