## Assignment of interventions: blinding

### Who will be blinded {17a}

This trial will not be blinded due to the nature of the intervention.

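### A single block size of 6, visible on site in an open one-clinic trial, lets anyone who tracks allocations know an expected 10.6 of 46 in advance

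*Protocol article*

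**What the plan says.** - **Block size.** Sequence generation {16a} of the protocol article assigns women "using a random block method of 6 that will be created by the website". One size is named.
- **Visibility.** Concealment mechanism {16b}: "Inside each envelope, 6 cards will be placed in the order of the sequence in each block", and "Block numbers will be written on each envelope". The same section plans "a sequence for the sample size 23 will be created" and "23 non-transparent envelopes and cards (as much as the total sample size) will be prepared".
- **Target.** Participant recruitment: "We aim to recruit 46 participants (23 individuals in each arm").
- **Openness.** Who will be blinded {17a}: "This trial will not be blinded due to the nature of the intervention". Study setting {9} places the trial at one clinic.
- **Who allocates.** Implementation {16c} has a dietitian and an obstetrician-gynecologist enrol, and continues: "Then, the dietitian will randomly stratified participants to receive either PLCD or KD". Sequence generation {16a} instead gives randomisation to an investigator who neither obtains nor enters participant data.
- **Stratification.** Trial design {8} and Study setting {9} call the randomisation stratified. No strata are named.

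**The concern.** In a balanced block of 6, each diet has three places. Once one diet has used its three, every remaining place in that block is known. Foreknowledge requires the block size, the block boundaries and the earlier allocations. Here the first two are on the envelopes. The third is open to clinic staff because nothing is masked, and dietitians deliver both diets and telephone every woman every two weeks.

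If the person who enrols can foresee the next diet, she can delay, hurry or discourage a particular woman, for example one who seems well motivated. The groups would then differ before treatment starts, on a trait that nobody records, and the primary outcome is weight loss. Covariate adjustment cannot reliably correct this.

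The point is separate from the envelope arrangement. Repairing the envelopes would leave the block length, and so the predictability, as it is.

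**Working it through.** **Inputs.** Block size 6, so m = 3 places per diet ({16a}); N = 46 at 1:1 (Participant recruitment); SDs 2.42 and 0.8 and a difference of 2 units (Sample size {14}). The plan gives no figure for predictability, so there is none to reproduce. Its step from 18 to 23 per arm does reproduce: 18 × 1.25 = 22.5, rounded up to 23.

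**1. Blocks in 46.** 46 = 7 × 6 + 4: seven full blocks and four places of an eighth.

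**2. Allocations certain in advance.** A 3:3 block has 20 orderings. The number of forced final places is 1 in 12 orderings, 2 in 6 and 3 in 2. The mean is (12×1 + 6×2 + 2×3)/20 = 1.5, which agrees with 2m/(m+1) = 6/4. In the eighth block the fourth place is forced only if the first three are alike, with probability 2/20 = 0.1.

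Total: 7 × 1.5 + 0.1 = **10.6 of 46 (23%)**. Each full block forces at least one, so the minimum is 7; 8 to 14 covers about 95% of lists. With two strata (sizes from 15/31 to 31/15) the expectation stays at 10.0 to 10.6.

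**3. Best guess.** The rule is to guess the diet that is behind and toss a coin when level. The chance of being right at places 1 to 6 is 0.5, 0.6, 0.6, 0.7, 0.7 and 1.0, which sums to 4.1. The first four sum to 2.4. Total: 7 × 4.1 + 2.4 = 31.1, and 31.1/46 = **68%**, against 23 (50%) by chance.

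**4. Final split.** Four places drawn from a 3:3 block split 2:2 in 12 of 20 orderings. So 23:23 occurs in 60% of lists and 24:22, one way or the other, in 40%. Power for a difference of 2 with the stated SDs (normal approximation, two-sided 0.05) is 96.4% at 23:23 and 95.9% to 96.9% at 24:22.

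**5. Alternatives at N = 46.** Certain allocations for varied blocks come from simulation, assuming the guesser knows which sizes are possible and counting only logical certainties. Their guess rates and splits come from a separate simulation of 60,000 lists. For the single ordering, 2m/(m+1) with m = 23 gives 46/24 = 1.9.

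| Scheme | Certain in advance | Best guess correct | Final split |
|---|---|---|---|
| Fixed 6 | 10.6 | 68% | 23:23 in 60%, else 24:22 |
| Varied 4/6 | about 2.6 | about 69% | 23:23 in about 78%, else 24:22 |
| Varied 4/6/8 | about 1.1 | about 68% | 23:23 in about 73%, nearly all others 24:22, rarely 25:21 |
| One ordering of 23 and 23 | 1.9 | 58% | always 23:23 if all 46 enter |

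Varying the size removes most of the certainty but not the advantage in guessing. Every block still returns to balance, so the running totals show which diet is behind.

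**The case against.** **Who would know.** {16a} names an independent investigator as randomiser, so a reader who takes it as established that the allocating dietitian knows about 11 allocations goes too far. The article also does not say that the dietitian who screens and the one who counsels are the same person. This stands, and 10.6 is conditional on someone holding the block size and the history. It does not remove the point: selection bias depends on what the enroller can foresee, whoever opens the envelope, and a dietitian enrols under {16c}.

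**Opportunity.** Eligibility is judged jointly with an obstetrician-gynecologist. Study setting {9} puts consent and cycle-timed blood tests before allocation, which makes timing a woman into a slot harder. This lowers the risk without closing it, and {16a} puts randomisation at the first visit.

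**Balance.** A reader might infer that blocks of 6 fail to deliver 23 per arm. They only fail to guarantee it; the worst split is 24:22 and power hardly changes.

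**Size of the bias.** It is tempting to convert predictability into kilograms. The documents give no basis for it: the answer depends wholly on an assumed selection effect and on whether the enroller acts on every guess or only on certainties. Sample size {14} also offers two yardsticks, 2 units and 3.14 − 1.66 = 1.48.

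**A larger defect nearby.** As written, opening a six-card envelope could expose a whole block, and the sequence and envelope counts of 23 do not fit 46 women. That is the more serious concealment problem. The figure of 10.6 describes what would remain after it is repaired.

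**The wording.** The phrase in {16a} might be read as random block sizes. The six cards per envelope argue against that reading.

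**Conclusion.** The point holds as a moderate design weakness that should be corrected. With one block size of 6 at N = 46, an expected 10.6 allocations (23%, at least 7) are certain in advance and about 68% can be guessed. This assumes that the person concerned knows the block size and all earlier allocations. The open design, the single clinic and the numbered six-card envelopes make that plausible. The article does not show that anyone would exploit it, and no bias in kilograms should be claimed. The missing guarantee of 23:23 is immaterial. The two statements about who allocates contradict each other and must be reconciled.

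**What to change.** 1. In Sequence generation {16a}, replace the fixed block of 6 with randomly varied block sizes that are not disclosed to clinic staff. Sizes 4/6 cut the certain allocations to about 2.6, and 4/6/8 to about 1.1. Either can be used within strata. Keep the sizes out of documents that clinic staff see.
2. If no stratification is intended, say so and use one random ordering of 23 and 23. This also lowers the guess rate to 58%, which varied blocks do not. It cannot be stratified, and it balances less well if recruitment stops early. At 40 women (an assumption), 20:20 would occur in 33% of lists and a difference of 4 or more in about 19%.
3. Have the list generated and held by someone outside enrolment and counselling, who releases each allocation only after the woman is enrolled. Reconcile {16a} and {16c} accordingly.
4. In Concealment mechanism {16b}, remove the block numbers and the six-card envelopes, and correct the counts of 23 to match 46 women.

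The cost is one new list and a few sentences. Balance over calendar time may be slightly looser and, with a block of 8 or a single ordering stopped early, so may the final split. This matters little with one site and no interim analysis.

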#### Concealment mechanism {16b}

The following will be considered in the implementation of the random assignment process: (a) one English letter is assigned to each of the groups: A to the PLCD group, B to the KD group; (b) a sequence for the sample size 23 will be created; (c) for the concealment process of random allocation, 23 non-transparent envelopes and cards (as much as the total sample size) will be prepared. Inside each envelope, 6 cards will be placed in the order of the sequence in each block. Block numbers will be written on each envelope. The name of the desired group will be written on each card in sequence.

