### Trial design {8}

This is a parallel-arm, open, stratified randomized clinical trial. Forty-six overweight or obese women diagnosed with PCOS will be randomly stratified to receive either PLCD or KD for 8 weeks.

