### Sample size {14}

According to the formula, the standard deviation of weight in the dietary group of PLCD and KD would be equal to μ_1_ = 3.14 (σ_1_ = 2.42) and μ_2_ = 1.66 (σ_2_ = 0.8) respectively. In the following sample with *α* = 0.05, the sample size required to have 80% power to detect a difference of 2 units of change in weights would be 18 people in each group. Considering the possibility of 25% missing people in the follow-up, the sample size increases to 23 people in each group.$$n=\frac{{\left({z}_{1-\frac{a}{2}}+{z}_{1-\beta }\right)}^{2}+\left({\sigma }_{2}^{1}+{\sigma }_{2}^{2}\right)}{{\left({\mu }_{1}-{\mu }_{2}\right)}^{2}}$$

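### The allocation procedure cannot be carried out as written (23 against 46 women, six ordered cards per envelope) and does not secure concealment, and the sections on who assigns and when disagree

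*Protocol article*

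**What the plan says.** **Numbers.** Sample size {14} ends with "the sample size increases to 23 people in each group", and Participant recruitment confirms it: "We aim to recruit 46 participants (23 individuals in each arm". Concealment mechanism {16b} then says "a sequence for the sample size 23 will be created" and prepares 23 opaque envelopes and cards, a count it equates in brackets with the whole sample.

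**Envelopes.** The same section continues: "Inside each envelope, 6 cards will be placed in the order of the sequence in each block". Each envelope carries a block number. Sequence generation {16a} fixes the block size at 6, and Who will be blinded {17a} says that the trial is not blinded.

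**Who assigns.** Sequence generation {16a}: "Randomization will be conducted by an investigator who is not involved in obtaining or entering" participants' data. Implementation {16c} has a dietitian and an obstetrician-gynecologist enrol, and continues: "Then, the dietitian will randomly stratified participants to receive either PLCD or KD".

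**When.** Sequence generation {16a} places randomisation at the first visit. Study setting {9} has women screened at the clinic, sent to the laboratory for baseline blood tests, and allocated a diet only when they come back to the clinic.

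**Stratification.** Trial design {8}: "This is a parallel-arm, open, stratified randomized clinical trial". Study setting {9} repeats the label. Sequence generation {16a} and Concealment mechanism {16b} describe a single block list and name no factor.

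**The concern.** Concealment means that whoever decides whether and when a woman enters cannot know her diet beforehand. Here the enrolling dietitian is also said to assign, the envelope is opened for a whole block at once, and the trial is open with a stated block size. Someone who knows that the next card is the ketogenic diet could delay or bring forward a motivated or heavier woman. The primary outcome is weight loss in 46 women, so a few such decisions could shift the comparison. Differences in unmeasured motivation could not be reliably adjusted away afterwards. This does not show that bias will occur. It shows that the stated procedure lacks the safeguard against it, and that staff following the text would have to improvise on the count, on who assigns and on the timing.

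**Working it through.** **Step 1. Where 23 comes from.** Inputs from Sample size {14}: 18 per group and 25% loss. 18 × 1.25 = 22.5, rounded up to 23 per group. This reproduces the plan's 23 and shows that it is a per-arm number. Whether 18 is itself right does not matter here. Total = 2 × 23 = 46, as Participant recruitment says.

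**Step 2. What the trial needs.** 46 / 6 = 7.67, so 8 blocks, or 8 × 6 = 48 slots, the last block partly used.

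**Step 3. What Concealment mechanism {16b} provides.**

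| Reading | Allocations | Against 46 |
|---|---|---|
| Sequence of 23, taken literally | 23 (23 / 6 = 3.83, so 4 blocks, 24 slots) | 23 short |
| 23 envelopes × 6 cards | 138 | three times too many |
| 23 meant as per-arm | 46 | matches, but the text calls 23 the total |

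The sequence length and the card count within this one section cannot both be right.

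**Step 4. Exposure from six cards in one envelope.** Opening it for the first woman in a block leaves 5 of 6 allocations open to view, 5 / 6 = 83%. Over 46 women there are seven full blocks and one with 46 − 42 = 4 women, so at most 7 × 5 + 3 = 38 of 46 (83%) could be known in advance. This is an upper limit. It assumes that the cards are not individually sealed and that the person enrolling sees the opened envelope.

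**Step 5. Predictability with perfect single envelopes.** This assumes a known fixed block of 6 (3:3, 20 equally likely orders) in an open trial.

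- *Certain allocations.* The last j are certain if they all belong to one arm. Expected number = 1 + 8/20 + 2/20 = 1.5 of 6, or 25%.
- *Best guess* (always name the arm with more places left). Expected correct by position: 0.5 + 0.6 + 0.6 + 0.7 + 0.7 + 1.0 = 4.1 of 6, or 68.3%. Chance is 50%.
- *Mixed blocks of 4 and 6, same guessing rule.* A block of 4 gives 2.83 correct, so (2.83 + 4.10) / 10 = 69.3%.

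Varying the block size can therefore reduce certainty but does not lower the best-guess rate.

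**Step 6. Roles and timing side by side.** If the investigator in Sequence generation {16a} only generates the list, Implementation {16c} leaves the cards with someone who enrols. If that investigator also assigns, the two sections contradict each other. Randomising at the first visit cannot be squared with Study setting {9}, where allocation follows the laboratory baseline.

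**The case against.** The strongest reply is that the 23 is a slip and that this is a condensed article. The per-arm number was probably mislabelled. The custody of the envelopes and the sealing of the cards may be described in a full protocol. If the uninvolved investigator keeps the envelopes and draws cards in order, the dietitian never sees the next five. A fixed block of 6 is a common choice, and several sections use stratify loosely to mean assign.

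Much of this stands. A reader might infer that half the women have no randomisation sequence. That is only the literal reading of 23, and the 138 cards implied by the same section speak against it. A reader might also infer that 83% of allocations will be seen in advance, but that depends on handling the article does not describe. Nor does the 68% guess rate argue for mixed blocks (Step 5).

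The reply does not remove what the article does state: a wrong total, an incompatible card count, a block of allocations in one envelope, two answers on who assigns and two on when. A slip in the count would not explain the shared envelope. The stratified label is also not only loose usage, since Trial design {8} and Study setting {9} apply it to the design itself.

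**Conclusion.** The point holds as a procedure that cannot be followed as written and that does not secure concealment. The count error is certain: 23 is called the total where 46 are randomised, and 23 envelopes of six cards hold 138 allocations against 46 needed. The most likely explanation is a per-arm number in the wrong place, which is easily corrected.

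The concealment weakness is conditional in size. Up to 5 of 6 allocations can be exposed when an envelope is opened, if the cards are not separately sealed and the enroller has sight of them. The article offers no protection against either, and Implementation {16c} points towards the enroller having sight of them, taking the dietitian who enrols and the one who assigns to be the same person. The conflicts over the assigner and over the timing rest on the text alone. The stratified label has no factor behind it in this document. None of this establishes that selection has happened or will happen. It should be settled before the first allocation. If recruitment has already begun, the procedure actually used should be documented.

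**What to change.** 1. In Concealment mechanism {16b}, replace the sequence of 23 with one list of 46 to 48 allocations (8 blocks of 6 give 48).
2. Put one allocation in each sequentially numbered, opaque, sealed envelope, with no block number on it.
3. Have the investigator named in Sequence generation {16a} hold the envelopes and release each only after the woman is irrevocably enrolled and her baseline assessments are complete.
4. Remove assignment by the dietitian from Implementation {16c}.
5. Align Sequence generation {16a} with Study setting {9}, so that both place randomisation after baseline.
6. Delete the word stratified, or state the factor actually used, keep a separate list for each level and include the factor in the analysis.

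Undisclosed, varied block sizes are optional. They make it harder to know an allocation with certainty (25% on average under a known fixed block of 6), but they leave the best-guess rate at about 68 to 69%.

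The cost is about 48 envelopes and the investigator being reachable at each allocation, which the article does not currently promise. Stopping at 46 with blocks of 6 can leave a 24:22 split (40% of lists, since the last block is cut at four). The present block size already carries that, so the fix does not add it.

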#### Implementation {16c}

The investigator who collects the information is unaware of the type of allocation of the samples to the study groups. The participants will be enrolled to the study by both a dietitian and an obstetrician-gynecologist according to the eligible criteria. Then, the dietitian will randomly stratified participants to receive either PLCD or KD.

## Assignment of interventions: blinding

### Who will be blinded {17a}

This trial will not be blinded due to the nature of the intervention.

### Procedure for unblinding if needed {17b}

This trial will not be blinded due to the nature of the intervention.

## Data collection and management

### Plans for assessment and collection of outcomes {18a}

#### Baseline measures

After the screening, the demographic characteristics questionnaire, the physical activity questionnaire (IPAQ), the Ferriman-Gallwey score, and health-related quality of life (SF-36) as well as 3-day food records questionnaires will be completed. Furthermore, all participants will undergo baseline assessments. Biochemical analysis and anthropometric measurements include FBS, insulin level, lipid profile (cholesterol, triglycerides, LDL, and HDL), sex hormones (testosterone, LH, FSH, and DHEA) during the beginning of the follicular phase (days 3–8 of the menstrual cycle), weight, height, weight, waist circumference, hip circumference, waist-to-hip ratio (WHR), and body composition indices (fat body mass (FBM), lean body mass (LBM)). Also, body mass index (BMI) and HOMA-IR will be calculated according to their formula. Serum levels of blood ketone bodies (KBs) will be assessed to ensure they are not in ketosis phase at the beginning of the study.

Anthropometric

Body weight, high, waist circumference, and hip circumference will be determined by a proficient research assistant at the Fatahi Clinic. Body weight will be measured with the subject wearing light clothing, shoes, and socks removed, to the nearest 0.1 kg using an electronic scale with bioimpedance analysis (Plus Avis 333 Body Analyzer, China). Hight will be determined to the nearest 1 cm using a well-mounted portable stadiometer (Holtain Ltd, UK), body mass index (BMI) will be calculated in Kg/m^2^, waist circumference will be measured after removing clothes from the abdomen, as the smallest circumference between the lowest rib and the iliac crest on the midaxillary line, the hip circumference will be determined at the level of the widest circumference over the great trochanters, and waist-to-hip ratio will be calculated as waist measures divided by hip measurement [29].

Body composition analysis as muscle mass (MM), body fat mass (FM), percent body fat (PBF), and total body water (TBW) will be expressed in kilograms, while total energy expenditure (TEE) will be reported in Kcal and will be analyzed using an electronic scale with bioimpedance analysis (Plus Avis 333 Body Analyzer, China). All parameters will be measured before and two months after the diet intervention.

2.Blood sampling and collection

After at least 10 h of fasting, 10 ml venous blood sample will be drawn by venous puncture from the bronchial vein of the participants to assess fasting blood sugar (FBS), insulin level, sex hormones, and lipid profile. Luteinizing hormone (LH), follicle-stimulating hormone (FSH), dehydroepiandrosterone sulfate (DHEA), testosterone, and insulin levels will be evaluated by immunochemiluminescent method, blood glucose by the enzymatic method with hexokinase, total cholesterol, high-density lipoprotein (HDL), low-density lipoprotein (LDL), and triglycerides by enzymatic colorimetric assay. The hormonal status evaluation will be performed during the follicular phase of the menstrual cycle, between the first and the seventh day. The Homeostatic Model Assessment (HOMA-IR) index will be calculated according to the formula (insulinemia mU/ml × glycemia mg/dL/450). After the first evaluation, patients will undergo the intervention, until the end of 2 months when they will be re-evaluated in the same way. All biochemical tests will be assessed clinically at the Reference Laboratory of Kermanshah University of Medical Sciences.

3.Ferriman-Gallwey score

Hirsutism is considered as one of the common clinical symptoms of polycystic ovary syndrome which is due to hyperandrogenism. It is estimated that 70% of women with PCOS also manifest hirsutism symptoms. Hirsutism is evaluated by the Ferriman-Gallwey score [30, 31].

4.Quality of life questionnaire

The quality of life questionnaire for women with polycystic ovary syndrome has been validated previously and used to both determine the psychological impact of having PCOS and the effect of participation in the intervention [30, 32]. Thus, it will be used in this study with the same purpose.

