#### Secondary outcomes

The secondary outcomes are including body mass index (BMI), fat body mass (FBM), lean body mass (LBM), body fat percentage, waist circumference, insulin level as well as sex hormones (testosterone, LH, FSH, DHEA), lipid profile (cholesterol, triglycerides, low-density lipoprotein (LDL), high-density lipoprotein (HDL)), glucose levels, HOMA index – IR, physical activity, health-related quality of life (SF-36), and Ferriman-Gallwey score, before and after the intervention.

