## Statistical methods

### Statistical methods for primary and secondary outcomes {20a}

Data analysis will be done using SPSS Statistics (version 19, NY, USA). A two-tailed statistical significance will be accepted at *P* < 0.05. Each outcome variable assessed will be analyzed according to diet (PLCD or KD) and time (before and after each diet) using a repeated-measures two-way analysis of variance (ANOVA). Where appropriate, a Student–Newman–Keuls post hoc test will be used to assess the origin of any significant differences detected by the ANOVA models. Variables will be adjusted for potential confounders which will be determined using multiple linear regressions.

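### The printed HOMA-IR formula divides by 450 instead of 405 and labels insulin mU/ml, so values calculated as written would be 10% too low

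*Protocol article*

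**What the plan says.** The item on blood sampling, within Plans for assessment and collection of outcomes {18a}, fixes the calculation: the index will be "calculated according to the formula (insulinemia mU/ml × glycemia mg/dL/450". The same item has participants measured again in the same manner at two months, so the formula applies at both time points.

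The only other reference to the calculation is earlier in that section, where "body mass index (BMI) and HOMA-IR will be calculated according to their formula". It gives no constant and no unit, so it neither corrects nor contradicts the printed formula.

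HOMA-IR is part of one of the listed objectives {7} and is a secondary outcome ("glucose levels, HOMA index – IR, physical activity, health-related quality of life (SF-36), and Ferriman-Gallwey score, before and after the intervention"). Under Statistical methods {20a}, each outcome is analysed by diet and time "using a repeated-measures two-way analysis of variance (ANOVA".

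**The concern.** The protocol names an established index, so its constant is not a free choice: it follows from the units of insulin and glucose. A divisor of 450 does not match glucose in mg/dL, and mU/ml is not a unit in which fasting insulin is expressed for this index.

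Insulin resistance is central to the trial's rationale, and earlier reports of improved HOMA-IR are part of the case for the ketogenic diet. If the printed formula is followed, the trial's HOMA-IR results will be on a scale of their own. They could not be set beside that literature, pooled as raw mean differences, or read against a published cut-off. A 10% error is also hard to notice, because the values still look plausible.

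**Working it through.** **Inputs from the protocol.** Divisor 450, insulin in mU/ml, glucose in mg/dL (section {18a}, blood sampling).

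**Inputs from outside the protocol.** The standard definition of HOMA-IR, insulin (µU/mL = mU/L) × glucose (mmol/L) / 22.5, and the glucose conversion, 1 mmol/L = 18 mg/dL (18.0156 from a molar mass of 180.156).

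**Step 1: the divisor for mg/dL.** 22.5 × 18 = 405, or 22.5 × 18.0156 = 405.35 with the unrounded conversion. To arrive at 450, the conversion would have to be 450/22.5 = 20 mg/dL per mmol/L, which is not the value for glucose.

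**Step 2: can 450 be reproduced with other units?**

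| Insulin | Glucose | Divisor |
|---|---|---|
| µU/mL | mmol/L | 22.5 |
| µU/mL | mg/dL | 405 |
| pmol/L (6.0 per µU/mL) | mmol/L | 135 |
| pmol/L (6.0 per µU/mL) | mg/dL | 2430 |
| pmol/L (6.945 per µU/mL) | mg/dL | 2813 |

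None gives 450.

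**Step 3: size of the error from the divisor.** Printed value / standard value = 405/450 = 0.900 (405.35/450 = 0.901). The ratio is the same for every participant and visit.

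**Step 4: the insulin unit.** 1 mU/ml = 1000 µU/mL. Entering insulin literally in mU/ml divides the index by 1000. Together with the divisor the factor is 0.90/1000 = 0.0009, about 1111-fold too low.

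**Step 5: illustration with assumed inputs.**

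| Insulin (µU/mL) | Glucose (mg/dL) | Divisor 405 | Divisor 450 | 450 and literal mU/ml |
|---|---|---|---|---|
| 10 | 90 | 2.22 | 2.00 | 0.0020 |
| 20 | 100 | 4.94 | 4.44 | 0.0044 |
| 25 | 105 | 6.48 | 5.83 | 0.0058 |

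**Step 6: effect on inference.** A constant factor scales a difference and its standard error alike. In simulated data with 18 per arm, multiplying all values by 0.9 moved the mean difference from 0.316 to 0.285. It left the t statistic (0.748), its p-value (0.460) and the Mann–Whitney p-value (0.091) as they were. By the same argument the ANOVA F statistics, percentage changes and standardised effects do not move.

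**The case against.** The strongest reply is that this is probably a misprint with little consequence inside the trial. The document cannot show whether 450 is in the working formula or only in the article. HOMA-IR is one of many secondary outcomes. Eligibility does not depend on it, and the protocol sets no HOMA-IR cut-off or responder definition. The primary outcome and the sample size rest on weight. No test of which diet lowers HOMA-IR more could change. Fasting insulin and glucose are measured and reported in their own right, so the index can be rescaled at any time by 450/405 = 1.11. The thousandfold reading is unrealistic, because the laboratory would report in its usual unit and values near 0.002 to 0.006 would be caught immediately. Finally, neither 22.5 nor 405 appears in the protocol.

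Most of this stands, and it limits how serious the point is. It does not make the formula right. The 10% bias is conditional on the formula being applied as printed, but it is the only formula the protocol gives and nothing elsewhere corrects it. The reference value is external only in the sense that it is the definition of the index the protocol names, combined with a unit conversion; it is not a disputed result from another study. Even if the analysis file is correct, anyone who follows the published text will get wrong values.

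**Conclusion.** The formula is wrong as written. Followed literally for the divisor, it gives 0.90 of the standard HOMA-IR, so means, standard deviations, absolute changes, absolute diet differences and confidence limits are all 10% too low. The insulin unit is mislabelled by a factor of 1000. That is most likely a slip for µU/mL or mU/L and matters in practice only if taken literally.

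The conclusion rests on the standard definition of HOMA-IR and on 18 mg/dL per mmol/L for glucose; using 18.0156 changes the factor only to 0.901. The damage is confined to the absolute scale of one secondary outcome and to comparisons outside the trial. The comparison of the two diets by significance test, the primary outcome and the power are untouched. It should be corrected, but it does not threaten the trial's main conclusion.

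**What to change.** Restate the formula as fasting insulin (µU/mL, i.e. mU/L) × fasting glucose (mg/dL) / 405. Confirm the unit in which the laboratory reports insulin, and check that the analysis file uses the same unit and divisor. If any values have already been calculated with 450, multiply them by 450/405 or recompute them from the stored insulin and glucose results. The cost is one number and one unit in the text plus a check of the computation; no new data are needed.
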